## Abstract

**Background:**

Sexual health is often underaddressed in cancer care, especially among survivors of breast and gynecological cancer. In Colombia, treatment side effects, cultural stigma, and limited training among health care providers affect well-being. Although international guidelines promote patient-centered and culturally sensitive approaches, few interventions have been implemented in low- and middle-income settings.

**Objective:**

This study aimed to describe the feasibility and acceptability of an educational psychosexual intervention for survivors of breast and gynecological cancer, including design, integration of qualitative and quantitative methods, core components, measurement time points, and a prespecified analysis plan.

**Methods:**

This is a prospective, single-group feasibility study at a university hospital in Colombia. Participants are adult women who completed treatment for breast or gynecological cancer at least 2 years before enrollment. The intervention combines tiered educational workshops, semistructured group interviews, and optional individualized counseling. Qualitative data will explore perceptions, barriers, and facilitators related to sexual health and well-being. Quantitative outcomes include the Female Sexual Function Index and European Organisation for Research and Treatment of Cancer Quality of Life Questionnaire Core 30 before and after the intervention to estimate change. Pre- and postintervention scores will be compared with paired tests and CIs. Qualitative data will undergo reflexive thematic analysis. Mixed findings will inform feasibility, acceptability, and practical recommendations. The intervention was co-designed with survivors and a multidisciplinary team, refined by expert review and a manual, and pilot-tested to optimize acceptability, logistics, and fidelity.

**Results:**

The study was funded in December 2024 and approved by the Comité de Ética en Investigación Biomédica of Fundación Valle del Lili. Recruitment began in March 2025 and is expected to end in September 2025. As of July 2025, 13 participants had enrolled (n=2, 15.4% survivors of breast cancer; n=11, 84.6% survivors of gynecological cancer). Based on pretrial piloting, shorter session blocks and optional hybrid delivery were made available to support adherence while preserving core content and objectives. Final analysis is planned for October 2025, with results expected in December 2025.

**Conclusions:**

This protocol evaluates the feasibility and acceptability of a codesigned, context-adapted psychosexual education model. Findings will guide implementation refinements and the design of a future comparative study of effectiveness and longer-term outcomes and may inform sustainable integration of sexual health into survivorship care in low- and middle-income settings. The model is intended to be replicable and scalable across oncology and other chronic disease contexts.

## Introduction

### Background

Among patients with gynecological cancer, research has traditionally focused on oncological treatments aimed at prolonging overall survival and progression-free survival. However, quality of life is increasingly recognized as crucial for women who survive these diseases. Sexual health is a fundamental component of overall well-being and quality of life, yet it remains one of the most overlooked aspects of oncological care, especially among women who have survived gynecological cancers. A systematic review by Sousa Rodrigues Guedes et al [1] reported that 30% to 80% of women with cancer experience sexual dysfunction and that the likelihood of this condition is 2.7 to 3.5 times higher than in women without cancer.

In gynecological cancers, where organs directly involved in sexual function may be affected, the burden of sexual dysfunction is particularly high. For example, Firmeza et al [2] reported a 5% to 16% prevalence of dyspareunia after laparoscopic radical hysterectomy, and Jensen et al [3] found that among patients with cervical cancer receiving radiotherapy, 55% reported mild to severe dyspareunia and 30% were dissatisfied with their sexual life. In Colombia, survivors face additional barriers to sexual well-being, including physical treatment effects, psychological distress, cultural taboos, and limited training among health care providers [4-7]. Across gynecological cancers, surgery, pelvic radiotherapy, chemotherapy, and endocrine therapies contribute to decreased desire and arousal, vaginal dryness, dyspareunia, pelvic floor pain, body image disturbance, and relationship strain; recent reviews highlight multifactorial mechanisms (anatomical, neurovascular, hormonal, and psychosocial) and underscore the need for proactive assessment during survivorship care [8].

Beyond anatomical or physiological measures, such as vaginal dilators or estrogen gels, the psychosexual component is central to women’s sexual pleasure and recovery. Trials report benefits of psychosocial approaches: telephone counseling improved depressive symptoms and gynecological or cancer-specific concerns [9], and a nurse-led sexual rehabilitation program improved sexual function from 1 to 12 months after treatment [10].

Building on this, brief, structured clinician- and internet-delivered interventions have improved sexual concerns and communication, including a clinician communication pilot [11], documented patient preferences for routine discussion [12], and web-based psychoeducational programs (Fex-Can) under randomized evaluation [13,14]. Counseling frameworks such as PLISSIT (permission, limited information, specific suggestion, intensive therapy) and BETTER (bring up, explain, tell, time, education, record) provide practical, stepwise scripts for time-limited visits [15] and show comparative advantages [16], although the evidence base specific to survivors of gynecological cancer remains limited [9,10].

Worldwide, organizations such as the World Health Organization (WHO) [17]; the United Nations Educational, Scientific, and Cultural Organization [18]; and the World Association for Sexual Health (WAS) [19] advocate for integrated, patient-centered approaches that recognize sexual health as a fundamental right and an essential element of postcancer recovery. Despite these calls, translation into routine practice remains challenging in many low- and middle-income countries, where issues of access and cultural relevance persist [17,18]. Moreover, the evidence base is derived largely from high-income settings [20], motivating context-specific, culturally adapted interventions such as the one evaluated in this study.

This study is primarily designed to evaluate the feasibility and acceptability of implementing an educational psychosexual intervention for survivors of breast and gynecological cancer. As a secondary objective, it will estimate the preliminary effectiveness of the intervention. It is important to note that this is not a definitive effectiveness trial but an initial step to determine whether the intervention can be successfully implemented and is acceptable to participants.

### Protocol Objectives

This protocol aims to describe the feasibility and acceptability of implementing EDUSEXONCO—an educational psychosexual intervention for survivors of breast and gynecological cancer—including its design, mixed methods integration, intervention components, measurement time points, and prespecified analysis plan.

### Prespecified Study Aims

The primary aim is to describe the feasibility and acceptability of implementing an educational strategy to promote sexual health and quality of life in a cohort of Colombian patients (EDUSEXONCO project).

The secondary aims are to (1) estimate within-group change in sexual function (Female Sexual Function Index; FSFI) and health-related quality of life (European Organisation for Research and Treatment of Cancer Quality of Life Questionnaire Core 30; EORTC QLQ-C30) from baseline (before session 1) to after the intervention (end of session 3) and (2) explore the relationship between quantitative changes in FSFI and EORTC QLQ-C30 scores and qualitative findings on sexual well-being, communication, agency, and body image from baseline (before session 1) to after the intervention (end of session 3).

## Methods

### Design

This is a prospective, single-center, single-group (pretest-posttest) mixed methods feasibility study designed to evaluate the implementation and acceptability of an educational psychosexual intervention for survivors of gynecological cancer. Estimating preliminary effectiveness is a secondary objective. This is not a definitive effectiveness trial but an initial step to determine whether the intervention can be delivered successfully and is acceptable to participants.

This study uses an embedded convergent mixed methods design, giving equal priority to quantitative and qualitative strands. Quantitative data (FSFI and EORTC QLQ-C30 scores) will be collected at baseline (before session 1) and after the intervention (end of session 3). Qualitative data (focus groups, semistructured interviews, participant observation field notes, and anonymous diaries) will be gathered after each session. Integration will occur during interpretation through meta-inferences and joint displays that juxtapose pretest-posttest quantitative changes with qualitative themes related to sexual well-being, communication, agency, and body image. We will seek convergence, complementarity, and expansion; discrepancies will be examined to refine inferences and inform practical recommendations.

### Recruitment

#### Overview

We will use consecutive sampling from survivorship and gynecological oncology outpatient clinics. Procedures include (1) weekly electronic medical record prescreening (diagnosis, treatment completion of ≥2 years, age of ≥18 years, and active follow-up), (2) clinician referral during routine visits via a standardized slip, (3) approach in the clinic or telephone or email contact within 7 days, (4) brief scripted eligibility confirmation, and (5) provision of written informed consent (in Spanish). A recruitment log (approached, eligible, provided consent, and ineligible; reasons for decline; and dates) will quantify feasibility. Retention supports include flexible scheduling, reminders 48 to 72 hours before sessions, and transportation provided for participants who require it (funded by the study grant and arranged by the research team in coordination with institutional services).

#### Recruitment Setting

The study will take place at Fundación Valle del Lili (FVL), a university-affiliated tertiary hospital in Cali, Colombia, recognized as a leading center for high-complexity care, including oncology services, in Latin America. FVL provides coverage across southwestern Colombia, serving a population with significant ethnic diversity, and maintains agreements with multiple health plans. Since 2017, the institution has operated a functional cancer unit dedicated to delivering comprehensive care for patients with oncological diseases. This unit offers facilities and procedures for initiation, follow-up, and monitoring of cancer treatment supported by an experienced multidisciplinary team [21]. The study will be conducted from 2024 to 2025 within this setting.

#### Study Population

Participants will be adult women (aged ≥18 years) who have survived breast or gynecological cancer (cervical, uterine, vaginal, vulvar, or ovarian), completed oncological treatment at least 2 years prior to enrollment, and remain under follow-up at FVL.

### Eligibility Criteria

The eligibility criteria are shown in Textbox 1.

Textbox 1.Eligibility criteria.
**Inclusion criteria**
Women aged ≥18 yearsHistory of breast or gynecological cancer (cervical, uterine, vaginal, vulvar, or ovarian)Completion of primary oncological treatment ≥24 months before enrollment (ongoing endocrine therapy or topical vaginal estrogen is allowed)Being disease free or having stable disease not requiring urgent oncological treatment as per the most recent clinic noteActive follow-up at Fundación Valle del LiliBeing Spanish speaking and able to complete study proceduresAbility and willingness to provide written informed consent and attend the 3 intervention sessions (in person or hybrid)
**Exclusion criteria**
Cognitive impairment that prevents informed participation (clinician judgment or Mini-Cog <3 if uncertain)Medical or psychiatric instability that would compromise safe participation (eg, uncontrolled pain crisis, acute severe depression with suicidality, or psychosis) per the treating clinicianActive cancer recurrence requiring immediate treatment at screeningAny condition that, in the investigator’s judgment, precludes group participation (eg, major morbidity or infectious isolation requirements) or completion of study assessmentsConcurrent enrollment in another sexual health behavioral intervention study

A brief operational screening checklist is provided in Multimedia Appendix 1.

### Intervention

EDUSEXONCO is a structured psychoeducational program to enhance sexual health and quality of life in survivors of gynecological cancer.

The intervention targets modifiable psychosexual determinants—knowledge, communication, agency, body image, dyspareunia self-management, and pelvic floor function—through evidence-based education, brief skill practice, and optional individualized counseling to support recovery of sexual well-being.

Materials include a facilitator manual (objectives and scripts for sensitive topics), slides and handouts, 3D anatomical models, fidelity checklists, attendance and adherence logs, and brief take-home practice sheets. Delivery comprises three components: (1) large-group theoretical-practical workshops organized in 3 progressive levels (basic, intermediate, and advanced), (2) semistructured group interviews (6‐8 participants) to elicit lived experience and contextual barriers and facilitators, and (3) optional individual counseling when chosen. Brief skills (communication drills, breathing and relaxation, and pelvic floor basics) are embedded in each session.

EDUSEXONCO is delivered as a sequence of 3 progressive theoretical-practical workshop levels (basic, intermediate, and advanced) to support gradual learning and skill acquisition. Each level includes two complementary strands: (1) a medical-sexual strand focused on anatomy and sexual response, treatment-related sexual changes, symptom self-management (eg, lubrication, pain, and dyspareunia), and safe use of supportive resources; and (2) a sociopsychological strand focused on stigma reduction, communication, consent and boundaries, self-compassion and body image, emotional regulation, and social reintegration. Each workshop incorporates brief guided practice (eg, “anatomy tour” using 3D models, communication scripts, sensate focus–inspired exercises, paced breathing, pelvic floor downtraining, and gentle yoga and relaxation), a take-home task to reinforce learning between sessions, and fidelity markers (eg, coverage of key items, completion of role-plays or practice, and delivery of handouts) to standardize delivery across facilitators. The full-day schedule is provided in Multimedia Appendix 2. A detailed topic-by-level syllabus including objectives, key content, practices, materials, leads, take-home tasks, fidelity markers, and qualitative prompts is provided in Multimedia Appendix 3. Examples of the semistructured interview guide are provided in Multimedia Appendix 4.

In-person group delivery takes place in education or rehabilitation rooms with acoustic privacy at FVL comprising 3 sequential full-day sessions (approximately 8 hours each) over approximately 3 weeks (roughly 24 hours in total). The intervention includes optional home practice for 10 to 15 minutes per day.

Language and examples are culturally adapted to Colombia, alternatives are provided for participants without a partner, activities are adapted for pain or mobility limitations, and Spanish-language materials target approximately B1 to B2 readability.

Fidelity is monitored using per-session checklists covering objectives, core activities, materials, timing, inclusivity, skill practice, and end-of-session outputs (anonymous diaries). Attendance and adherence logs capture session-level participation (sessions 1‐3), completion of pretest and posttest questionnaires, participation in the group interview and optional 1:1 counseling, and take-home practice reporting.

Usual care is allowed (gynecology, psycho-oncology, pelvic floor therapy, and analgesia). Cointerventions (eg, topical estrogen, dilators, and sex therapy) are documented. Adverse events (eg, pelvic pain flare or marked emotional distress) are recorded and managed via institutional pathways; urgent cases are referred to psycho-oncology immediately.

A multidisciplinary team will deliver and evaluate the intervention. All facilitators will complete a 2-hour orientation on the facilitator manual, stigma-free and rights-based communication, trauma-informed practices, confidentiality, and use of fidelity tools (presession and per-session checklists). Interviewers will receive additional coaching on qualitative interviewing and reflexivity memoing. Each professional involved in the study will assume 2 primary roles: participation in the theoretical-practical workshops according to their field of expertise and moderation or support during semistructured interviews focusing on topics related to their professional area. The team comprises the following members:

Principal investigator and study clinician (internist or gynecological oncologist)—oversees protocol fidelity and participant safety, addresses medical queries arising from workshops or interviews, and adjudicates eligibility or adverse event decisions as needed.Sexual health physician and sexologist—leads medical-sexual content on postcancer sexual physiology and function, pleasure, autoeroticism, and nonpharmacologic pain or dyspareunia strategies and provides brief one-to-one counseling when indicated.Psychologist—facilitates sessions on emotions, anxiety management, self-esteem, body image, and stigma; moderates group interviews; and manages emotional crises and referral to psycho-oncology per institutional pathways.Social worker—addresses sociocultural and socioeconomic barriers, family and social support networks, and reintegration and identifies cases requiring individualized follow-up or referral.Pelvic floor physical therapist—teaches basic pelvic floor contraction and relaxation, breathing, and posture for pain modulation; clarifies rehabilitation questions; and links exercises to sexual function.Nutritionist—provides guidance on nutrition to support recovery, energy, and quality of life; answers participant questions; and aligns advice with medical care.Yoga and relaxation instructor—leads brief, adapted breathing and posture practices to support emotional and physical well-being and offers alternatives for pain or mobility limitations.Sex educator—delivers comprehensive sexual education (communication skills, sexual aids, and diverse expressions of sexual health) using inclusive, culturally appropriate language.Data collection specialist and qualitative research assistant—manages audio recordings, field notes, deidentification, and secure transfer for transcription; maintains recruitment and fidelity logs; and supports postsession reflexivity memos.

### Role Boundaries and Safety

Companions may attend large-group workshops when desired by the participant but do not join interviews or individual counseling. Only trained team members deliver content in their scope; urgent clinical or emotional issues are escalated to the study clinician and psycho-oncology. All adverse events are documented and handled per institutional policy.

### Measures and Outcomes

The primary objective is feasibility and acceptability. We will quantify feasibility (eligibility, invitation, consent, recruitment rate, retention, attendance and adherence, fidelity, and data completeness) and acceptability (postsession satisfaction, perceived usefulness, and comfort; recommendation item scored from 0‐10). A priori thresholds are as follows: retention of ≥80%, attendance of ≥80% per session, fidelity of ≥80%, data completeness of ≥85%, no serious adverse events, acceptability mean of ≥4.0/5, and net promoter score of ≥30.

As a secondary objective, this study assesses quantitative outcomes using validated psychometric tools and qualitative dimensions using reflexive thematic analysis. Mixed methods integration will offer a comprehensive understanding of EDUSEXONCO’s effects on sexual rehabilitation and psychosocial recovery.

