### Sample Size

The quantitative pretest-posttest sample size was calculated based on mean differences and an adjusted SD of 0.69, informed by prior studies such as Starting the Conversation, a pilot trial using the FSFI to assess sexual function in survivors of gynecological cancer [11]. Assuming a moderate effect size (*d*=0.5), a 95% confidence level, and 80% power, the estimated sample size is 60 participants. Calculations were performed using G*Power (Heinrich Heine University Düsseldorf), a standard tool for sample size estimation in mean difference studies.

For the qualitative strand, sample adequacy is guided by the information power principle—considering study aim, sample specificity, quality of dialogue, and analytic strategy—rather than numeric saturation targets [24]. We purposefully seek heterogeneity in survivorship stage and symptom profiles to capture a range of experiences relevant to sexual health education.

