## Results

This study is funded by the Women’s World Banking Colombia Foundation, awarded in December 2024, and received ethics approval from FVL. Recruitment began in March 2025 and is planned until September 2025. As of July 2025, a total of 13 participants have been enrolled (n=2, 15.4% with breast cancer and n=11, 84.6% with gynecological cancer). During feasibility activities, full-day sessions were identified as a potential barrier to attendance; accordingly, contingency adaptations (shorter session blocks and optional hybrid delivery) were suggested and will be considered as needed without altering protocol objectives or core content. Quantitative and qualitative data analysis is scheduled for October 2025; final results are expected by December 2025.

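### Recruitment is a listed feasibility outcome with no threshold: every stated criterion can be met however few women enrol, while the article's own count projects to about a third of its target of 60

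*Protocol article*

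**What the plan says.** All references are to the protocol article.

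- **Outcomes.** Measures and Outcomes, under the primary objective: "We will quantify feasibility (eligibility, invitation, consent, recruitment rate, retention, attendance and adherence, fidelity, and data completeness").
- **Thresholds.** The same paragraph continues: "A priori thresholds are as follows: retention of ≥80%, attendance of ≥80% per session, fidelity of ≥80"%. The list ends with data completeness of at least 85%, no serious adverse events, mean acceptability of at least 4.0 out of 5, and a net promoter score of at least 30. Eligibility, invitation, consent and recruitment rate have no threshold.
- **Recruitment data.** Recruitment (Overview) sets up a log of women approached, eligible and consented, with reasons for decline and dates. The Dissemination and Implementation Plan puts recruitment first among the implementation outcomes. Neither gives a criterion.
- **Target.** Sample Size: "a 95% confidence level, and 80% power, the estimated sample size is 60 participants". The inputs are "Assuming a moderate effect size (*d*=0.5") and a size "calculated based on mean differences and an adjusted SD of 0.69". The article does not say on which scale d is defined or what the SD is the SD of.
- **Progress.** Results: "Recruitment began in March 2025 and is planned until September 2025"; "As of July 2025, a total of 13 participants have been enrolled". Analysis is scheduled for October 2025. No extension, revised target or rule for a shortfall appears.

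**The concern.** Feasibility is the primary objective, and whether the centre can enrol these women is part of it. The article chose to print its thresholds, so this is not detail held over to another document. It set criteria for what happens after enrolment and none for the four pre-enrolment outcomes it had just listed. The omitted element is also the one that its own count shows far off target.

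The Dissemination and Implementation Plan and Future Directions say that the results will guide a comparative, multisite study. For that study, a centre enrolling about a third of its planned number is central information. A report that all the stated thresholds were met would not register it.

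A second, smaller matter is the power statement. It stands unchanged beside an enrolment count that makes 60 very unlikely, and its inputs are not defined well enough to say what power a smaller sample would have.

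**Working it through.** **1. Can the thresholds be met at any N?** Retention, attendance and data completeness are proportions among enrolled women or their expected records. Fidelity is a proportion of session content delivered. Acceptability and net promoter score are summaries among respondents. The safety criterion is an absence of events. None contains the number enrolled, approached or consenting, so none fails because N is small.

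**2. Projected enrolment.** Inputs from Results and Sample Size: 13 enrolled, March to September 2025, count dated July, target 60. Projection = 13 / (months elapsed) × (months in window), assuming constant pace.

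| Reading of the dates | Rate per month | Projected N | Share of 60 | Rate needed for the other 47 | Ratio |
|---|---|---|---|---|---|
| 1 March to 31 July, close 30 September | 13/5 = 2.6 | 2.6 × 7 = 18.2 | 30% | 47/2 = 23.5 | 9.0 |
| 1 March to 1 July, close 30 September | 13/4 = 3.25 | 3.25 × 7 = 22.8 | 38% | 47/3 = 15.7 | 4.8 |
| Lowest: 1 March to 31 July, close 1 September | 13/5 = 2.6 | 2.6 × 6 = 15.6 | 26% | 47/1 = 47 | 18.1 |
| Highest: 31 March to 1 July, close 30 September | 13/3 = 4.33 | 4.33 × 6 = 26.0 | 43% | 47/3 = 15.7 | 3.6 |

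The main range is 18 to 23 and the widest is 16 to 26. Even the most generous reading needs 3.6 times the observed pace.

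**3. The stated sample size.** Paired t test, two-sided 0.05, 80% power, dz = 0.5:

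- Normal approximation: (1.960 + 0.842)² / 0.5² = 7.849 / 0.25 = 31.4, so 32 pairs.
- Exact noncentral t: power is 79.5% at 33 pairs and 80.8% at 34, so 34 pairs.
- At 60 pairs, power is 97%.

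The stated 60 is not reproduced. One calculation that gives it treats 0.5 as a raw difference, 0.69 as its SD, and the data as two independent groups: 2 × 7.849 × (0.69/0.5)² = 29.9, so 30 per group and 60 in total. That is not this design.

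If 0.5 is a raw difference and 0.69 the SD of the paired differences, dz = 0.5/0.69 = 0.72, and 17 pairs give 80%.

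**4. Power and precision at the projected N** (paired t, two-sided 0.05). The 95% CI half-width for the mean change is t(0.975, n−1)/√n, in units of the SD of the differences.

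| Pairs | Power, dz = 0.5 | Power, dz = 0.72 | CI half-width |
|---|---|---|---|
| 14 (80% of 18, rounded down) | 41% | 71% | 2.160/√14 = 0.58 |
| 18 (also 80% of 23, rounded down) | 52% | 83% | 2.110/√18 = 0.50 |
| 23 | 63% | 91% | 2.074/√23 = 0.43 |
| 60 | 97% | >99% | 2.001/√60 = 0.26 |

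The 80% is the retention threshold, used here as the lowest passing value. The half-widths do not depend on the reading of d.

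**The case against.** **No go/no-go rule exists.** The primary aim is to describe feasibility. Recruitment rate is a named outcome, the log will quantify it, and a shortfall against 60 would be visible in the report. A reader might infer that the plan will declare the intervention feasible on about a third of its sample and launch a comparative trial on that basis. The documents do not support this: no section combines the thresholds into a verdict, and results are said only to guide the design of a later study. What remains is that a plan which sets criteria for its feasibility outcomes sets none for the one its own data put in doubt, and gives no rule for a shortfall.

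**Power.** A reader might also infer that 80% power is lost because 60 will not be reached. That does not follow. With dz = 0.5 the requirement is 34 pairs. With dz = 0.72 it is 17, and 18 to 23 pairs would give 83% to 91% before attrition. The article does not say which reading it means, so neither a loss of power nor its preservation is established. Power also serves a secondary aim, and the article disclaims definitive effectiveness. This objection stands and makes power a subsidiary matter.

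**The projection.** Dates are given only to the month, and group-based delivery may make enrolment uneven. This widens the range to 16 to 26 but does not bring 60 within reach, and no surge is foreseen anywhere.

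**A late threshold.** Setting a pass mark such as 80% of 60 (48) after the July count would write in a foregone miss and tie it to a target that the paired inputs do not reproduce. This is right, and the fix below does not propose it.

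**Conclusion.** The point holds. All the printed thresholds can be satisfied at any number enrolled, although recruitment and consent rates are listed outcomes under the primary objective. Enrolment at the reported pace would end near 18 to 23 women, 30% to 38% of 60 (26% to 43% on the widest reading of the dates), assuming constant pace. The plan does not say what follows.

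The sample-size basis also needs restating. On paired data the stated inputs give 34 pairs or 17, depending on an undefined d and SD, and not 60. Power at 18 to 23 pairs is 52% to 63% with dz = 0.5 and 83% to 91% with dz = 0.72. After 20% loss it is about 41% to 52% and 71% to 83%. These figures are conditional on the reading and are secondary to the missing recruitment criterion.

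**What to change.** **Measures and Outcomes**

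- Add a criterion, or progression bands, for recruitment rate and for consent rate among eligible women. Derive them from what the later comparative study would need per site.
- Disclose that they were set after the July 2025 count.
- State that meeting the other thresholds does not by itself establish feasibility if recruitment falls short.

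**Sample Size**

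- Say whether d=0.5 is dz and what the SD of 0.69 refers to.
- Recompute the number for the paired design.
- Report power and CI width at the expected enrolment, conditional on that reading.

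**Cost.** Wording only, with no extra participants or assessments, since the recruitment log already collects the data. The feasibility statement becomes less favourable.
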